### Eligibility

Eligibility will be assessed using the WASH U KSADS [22]. This is a reliable and valid interview schedule used in research to confirm diagnosis and is carried out with the young person and his/her parent/carer. This eligibility assessment takes about 2–3 h to complete. Young people may participate if they meet the eligibility criteria and either are euthymic or have sub-threshold symptoms of an affective episode provided they are able to consent.

### Outcome measures

Most of the research studies on interventions in EOBD have focused their primary outcomes on clinical parameters such as symptomatic improvement, frequency of mood episodes and/or their duration, less need for hospitalisation or longer time spent in remission. Few studies have attempted to evaluate the intervention in terms of improvement in family functioning and/or health-related quality of life (HRQL). This mode of enquiry adopts a more patient-centred approach that focuses on the individuals’ perceptions of their physical, psychological and social functioning. An Australian study showed that children with mental health disorders were reported to have a worse HRQL than children with physical disorders and their problems interfered significantly with the daily lives of children, parents and family [23].

#### Validated quantitative questionnaires

##### The McMaster Family Assessment Device (FAD) [24]

The FAD is a 60-item, 4-point Likert-type questionnaire designed to evaluate families according to the McMaster Model of Family Functioning. It takes approximately 15 min to complete. It is made up of 6 scales which measure problem solving, communication, roles, affective responsiveness, affective involvement and behaviour control. In addition, there is a 12-item measure of general functioning that can be used as a global measure of family health/pathology [25]. It has good psychometric properties with good reliability and validity [26–28].

There are low correlations between FAD and the Marlowe-Crowne Social Desirability test, suggesting that the FAD responses are relatively free of the influence of social desirability [26]. This will be completed by parent/s.

##### Conflict Behaviour Questionnaire (CBQ) aka ‘Interaction Behaviour Questionnaire’ [29]

The CBQ is a self-report measure of problems with interpersonal behaviour between dyads (e.g. the mother about the adolescent or the adolescent about the father). Respondents answer true or false to questions about their relationship with a particular family member. The short form has 44 items and correlates 0.96 with the long version. It has been widely used [30, 31] and has adequate internal consistency and discriminant validity [29]. Both young people and one parent will complete this.

##### EuroQuol EQ-5D and EQ-5D-Y

EQ-5D is a standardised instrument for use as a measure of health outcome. The EQ-5D-Y is a youth version. It is developmentally appropriate and takes only a few minutes to complete. This will be completed by a young person and a parent. The EQ-5D descriptive system comprises 5 dimensions: mobility, self-care, usual activities, pain/discomfort and anxiety/depression. Each dimension has 3 levels: no problems, some problems, extreme problems. The EQ-5D-Y has the same basic system with some changes in wording. The EQ-5D is scored using UK population tariffs (a scoring system is under development for the EQ-5D-Y), which can be used in the calculation of quality adjusted life years (QALYs). QALYs are commonly used in economic evaluations.

##### Warwick Edinburgh Mental Well-being Scale (WEMWBS) [32]

This scale has been developed by Warwick and Edinburgh Universities to assess mental well-being. WEMWBS is a 14-item scale with 5 response categories, summed to provide a single score ranging from 14 to 70. The items are all worded positively and cover both feeling and functioning aspects of mental well-being. Its psychometric properties are robust and it is easy to complete [33]. This will be completed by the young person.

Self-completed baseline questionnaires will be given to the young person (3 in total, completion time, 30 min) and his/her family (3 for primary caregiver, completion time approx. 30 min), and an appointment for the research associate to collect these will be arranged. Assistance, via the CSO, will be offered to those who have difficulty filling them in. Once the questionnaires have been completed and returned, the randomisation procedure will occur. Randomisation will occur after baseline questionnaire completion as we do not want the type of treatment group allocation to bias questionnaire responses. Participants will be given a voucher (‘love to shop’) for £10 on completion of each batch of questionnaires (£30 in total). Participants and their families will complete these sets of questionnaires on 3 separate occasions, before randomisation, after treatment (at 6 months) and again after 12 months following randomisation.

### Randomisation

Participants will be randomised to ‘immediate treatment arm’ or ‘delayed treatment arm’ in a 1:1 ratio, using random permuted blocks. The randomisation allocation schedule will be generated by a statistician with no other involvement in the study. Randomisation will be performed by a trained member of the research team or CSO, using a secure password-protected Web-based system administered by Newcastle Clinical Trials Unit (https://apps.ncl.ac.uk/random). Randomisation will generate a unique 2-digit ‘study ID number’ for each participant.

### Interventions

#### Control condition: delayed treatment with treatment as usual

Families and the young person with bipolar disorder will receive usual care delivered by their referring Consultant Child and Adolescent Psychiatrist and the CAMHS team (usually a review appointment every 3–6 months). Families and young people will be offered the intervention after 1 year when all trial data collection is completed.

#### Intervention condition: immediate treatment

All family members living at home or involved in the care of the young person will be invited to attend the treatment and will receive 16 sessions of 1-h duration with a therapist over 25 weeks (1 therapist, 1 family unit). Treatment will be suspended if the young person becomes unwell as declared to the research team or Therapist by their referring Clinician.

The treatment structure includes:Seven weekly psycho-education sessions. During these sessions, the family and young person will be given information about the aetiology, treatment and self-management of BD. A relapse prevention plan and identifying early prodromal signs to lessen the impact and possible need for hospitalisation will be considered.Four fortnightly communication enhancement sessions will teach young people and their parents communication skills, offer positive feedback and active listening, make positive requests for change in others’ behaviour and give negative feedback.Four fortnightly problem solving skill training sessions encourage an open dialogue between family members about difficult topics and help all involved to develop strategies for solving these problems.A final overview session completes the intervention.

Participants will complete validated questionnaires, at baseline, immediately post intervention and again at follow-up after 6 months (T0, T6 and T12 months).

Treatment may take longer than 6 months if the young person becomes unwell. They will continue to get their therapy when they recover from an episode. If the T6 and T12 questionnaires are delayed by more than 6 months from the dates when they were meant to be completed, this will be considered as missing data. The young person and his/her family will be considered as a ‘dropout’ if he/she tells the research team that he/she no longer wishes to continue.

Families will be contacted by the research team on a monthly basis via text or email throughout the trial to be kept updated and to maintain good retention rates. On completion of the research study, young people will receive a certificate thanking them for their participation.

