**Methods/Design:**

The trial will examine the feasibility of a randomised, parallel group, non-blinded design and the procedures of a subsequent definitive trial. Thirty-three young people with BD and their families will be recruited. Participants will complete measures at baseline, on completion of the 6-month treatment and again after a further 6 months. The self-report measures include the Warwick Edinburgh Mental Well-being Scale, The McMaster Family Assessment Device (FAD), Conflict Behaviour Questionnaire aka ‘Interaction Behaviour Questionnaire’, EuroQuol EQ-5D-3L and EQ-5D-Y. Primary outcomes will be rates of eligibility, recruitment and retention, estimates of the variability in the self-report measures and assessment of the intervention delivery in the study population. Participants’ qualitative views on the measures and intervention will be sought to confirm the acceptability of intervention and study design. The health economics component will establish how cost-effectiveness will be assessed in a future definitive trial.

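### T6 and T12 are dated from the end of therapy in two places and from randomisation in a third, so follow-up timing in the immediate arm can depend on relapse and the lateness rule has no fixed start date

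*Protocol article*

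**What the plan says.** The follow-up schedule appears three times.

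- Abstract, Methods/Design: follow-up measures come "on completion of the 6-month treatment and again after a further 6 months".
- Intervention condition: immediate treatment: "Participants will complete validated questionnaires, at baseline, immediately post intervention and again at follow-up after 6 months (T0, T6 and T12 months".
- The paragraph after the WEMWBS description: "before randomisation, after treatment (at 6 months) and again after 12 months following randomisation".

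The first two date T6 from the end of therapy and T12 from six months beyond that. The third attaches a calendar month to T6 and counts T12 from randomisation.

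On therapy length, families "will receive 16 sessions of 1-h duration with a therapist over 25 weeks". The same section adds "Treatment may take longer than 6 months if the young person becomes unwell" and "They will continue to get their therapy when they recover from an episode". Participant compliance repeats the suspension rule and leaves the time of return to the treating clinician.

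The lateness rule in that section opens "If the T6 and T12 questionnaires are delayed by more than 6 months from the dates when they were meant to be completed" and goes on to class such forms as missing.

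The control section says that families in the delayed arm can take up FFT-A UK once a year has passed and the trial's data are all in. Quantitative data and analysis rules out formal comparison of the arms, allows descriptive contrasts, and carries confidence limits for SDs into sample size work for the definitive trial. Sample size considerations says that 30 patients serve to estimate variability at baseline.

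**The concern.** A follow-up time point should mean the same thing in both arms. If T6 means the end of therapy, an immediate-arm family whose therapy is suspended reaches T6 only after the young person has recovered enough to resume and has finished the sessions. A control family has no such date. Elapsed time, and possibly mood state at assessment, then depend on arm and on relapse.

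Three things are at stake:

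- the descriptive contrasts between arms at follow-up;
- any follow-up or change-score SD carried into the definitive trial's sample size;
- which forms count as missing, because lateness is measured from a due date that the protocol defines in two ways. Data completion (Design) and retention at follow-up (Participant compliance) are primary outcomes.

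The Design section says the study is to examine the design and procedures of the definitive trial, so an unresolved schedule could be carried forward.

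**Working it through.** **1. Planned therapy length.** The intervention section lists 7 weekly sessions, 4 + 4 fortnightly sessions and 1 final session: 7 + 4 + 4 + 1 = 16 sessions. The duration is 7 × 1 + 8 × 2 + 2 = 25 weeks, if the final session also follows a fortnightly gap (assumption). This reproduces the protocol's 16 sessions and 25 weeks.

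**2. Slack before month 6.** Six months is 6 × 365.25 / 12 / 7 = 26.09 weeks. Slack = 26.09 − 25 = 1.09 weeks, if therapy starts on the day of randomisation. Any delay in starting uses it up.

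**3. How the anchors separate.** Let s be the weeks of suspension, which the documents do not give. Therapy ends at week 25 + s, so under the therapy anchor T6 falls s − 1.09 weeks after calendar month 6. T12 moves by the same amount. Beyond about one week of suspension, every further week moves both.

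**4. Effect on the lateness rule.** As an illustration only, let therapy end at month 8, which is a suspension of 8 × 4.348 − 25 = 9.8 weeks (one month = 365.25 / 12 / 7 = 4.348 weeks).

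| | Therapy anchor | Randomisation anchor |
|---|---|---|
| T6 due | month 8 | month 6 |
| T6 last accepted | month 14 | month 12 |
| T12 due | month 14 | month 12 |
| T12 last accepted | month 20 | month 18 |

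A T6 form returned at month 13 is 5 months late and counts under the first anchor. Under the second it is 7 months late and missing. The same family thus gives different data-completion figures. Retention differs too, so far as it is counted from forms received in time; withdrawal is defined separately.

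Even on the randomisation anchor, T12 forms are accepted up to month 18, while the control section has data collection complete at 1 year. Those two statements also conflict.

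**5. Possible size at T6.** The documents give neither the share p unwell at month 6 nor their deficit D, in units of the SD when well, so both are assumed. Suppose every immediate-arm assessment that would have fallen in an episode is deferred until recovery, and no control assessment is. Then:

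- mean shift = p × D;
- control SD / immediate-arm SD = √(1 + p(1 − p)D²).

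| p | D | Mean shift (SD) | SD ratio |
|---|---|---|---|
| 0.05 | 0.5 | 0.025 | 1.006 |
| 0.20 | 1.0 | 0.20 | 1.077 |
| 0.30 | 1.5 | 0.45 | 1.213 |

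In the middle row, a sample size built on the smaller SD would be 1 / 1.077² = 0.862 of the right one, about 14% too low.

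**6. Set against sampling error.** The 95% confidence limits for an SD are √((n − 1)/χ²) times the estimate: 0.80 to 1.34 at n = 30, and 0.73 to 1.58 at n = 15 per arm. In most of the assumed scenarios the timing effect on the SD is smaller than this.

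**The case against.** The strongest reply is that the visits carry month labels, that the lateness rule speaks of dates on which forms were due, and that the WEMWBS paragraph gives month 6 and counts from randomisation for everyone. On that reading the schedule is already a calendar one and late forms are deviations with a cut-off. The reading is possible, but it does not remove the two statements that date follow-up from the end of therapy. The 6-month allowance, placed directly after the text on prolonged therapy, would still let a relapsing family's T6 wait until about month 12. No passage sets the controls' T6 date separately, so their calendar timing remains an inference from the WEMWBS paragraph and the control section.

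Four stronger readings are tempting, and the documents do not support them.

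- **Nobody in the immediate arm is measured in an episode.** Suspension depends on the referring clinician declaring illness. Resumption requires being well enough to take part, which is not stated to mean remission. Relapse after the last session, and mood state at T12, are untouched by the pause. Families without a suspension are not measured late at all.
- **The SDs for the definitive trial are biased.** The SD named under Sample size considerations is the baseline one, collected before randomisation, and timing cannot alter it. Only follow-up or change-score SDs could move, and uneven elapsed time might widen them.
- **The trial's result is biased by a known amount.** No formal arm comparison is planned, and the shift in step 5 is wholly assumed. It also treats instruments alike, including the parent-completed FAD, for which the protocol gives no deficit.
- **An episode lasts 10.2 weeks.** That Background figure is a recovery time from an index depressive episode in an earlier US trial. It is not a relapse length in young people enrolled in remission.

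Measuring at the end of therapy is a recognised choice, and the definitive trial will have its own protocol. Both points lower the weight of this one, but neither reconciles the text.

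**Conclusion.** The inconsistency is in the text and stands. Where therapy is suspended for more than about 1.1 weeks, the therapy anchor delays T6 and T12 in the immediate arm in a way linked to relapse, with no counterpart in controls. The firm consequence is an undefined due date for the 6-month lateness rule, and hence data-completion and retention figures that depend on which sentence is followed. The softer consequence is a possible bias in descriptive follow-up contrasts, probably towards the immediate arm at T6. Its size cannot be derived from the documents. The range of roughly 0.03-0.45 SD holds only under the assumed 5-30% unwell and 0.5-1.5 SD deficit, with every such assessment deferred. The baseline SD and the targets of 33 recruited and 50 approached are unaffected. This merits correction while recruitment is open, but it is not a critical flaw in a feasibility study without formal comparison.

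**What to change.** State one anchor for both arms: T6 and T12 fall 6 and 12 calendar months after randomisation, whether therapy is finished, suspended or not yet started. Measure the lateness window from those dates, and record the actual completion date of each form. At T6, record sessions attended and whether therapy is complete, and log the completion date when it comes. If an end-of-therapy score is wanted for late finishers, collect it as an additional descriptive assessment that does not replace T6. Align the Abstract, the WEMWBS paragraph and the intervention section, and reconcile the lateness window with the control section's statement that data collection is complete at 1 year. The rules for suspending and resuming therapy are not touched.

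The cost is protocol wording and a change to the questionnaire schedule. The downside is that some immediate-arm families will complete T6 before their last session, or while the young person is unwell.

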### Participant compliance

Where feasible, appointments will be arranged at the participants’ convenience at a NHS venue of their choice. Therapists will arrange clinical appointments and record which family members attend each session. Should a participant become unwell during the study, his/her intervention will be ‘suspended’ and he/she will resume therapy when he/she is well enough to participate in the FFT-A UK as determined by their treating clinician. The primary outcomes for this feasibility trial are rates of eligibility, recruitment, intervention delivery and participant retention at follow-up. These will be recorded on case report forms by the Trial Coordinator.

### Economic evaluation

A review of the existing health economics databases will be conducted to identify possible alternative measures of health state utility with young people with EOBD and their families. The search will be conducted in the two major health economic evaluation databases: NHS Economic Evaluation Database (NHS EED) and the Cost-Effectiveness Analysis Registry. NHS EED includes structured abstracts of quality-assessed full economic evaluations of health care technologies, with the only criterion for inclusion in the database is that the study is a full economic evaluation. The economic evaluations are selected as a result of hand searching journals, health technology assessment reports and electronic searches of CINAHL, Embase, MEDLINE and PsycINFO. Abstracts are prepared based upon the potential relevance of the study to the United Kingdom National Health Service (UK NHS), which is important as all health-related quality of life outcomes for this study should ideally have been used in the UK NHS setting (or a closely comparable alternative).

Additionally, this review will also use the Cost-Effectiveness Analysis Registry. This registry focuses on a particular type of economic evaluation—a cost utility analysis. This form of analysis requires measures of health-related quality of life, so it may be applicable to our review.

As a result of the review, we hope to identify the following:What tools have been used to gather health utility data in similar settings?Where were these tools used and are they potentially suitable for use in a multi-centre definitive trial?Key references from other researchers in the field if applicable to a UK NHS setting.

### Sample size considerations

No formal sample size calculation has been performed for this feasibility study as the primary outcome measures are concerned with the recruitment and randomisation to the trial and the acceptability of the trial in this population of patients. However, a sample size of *n* = 30 patients will provide sufficient data [35] to estimate the variability in the outcome measures at baseline and assess the feasibility of the trial. Data from a recent similar RfPB-funded study, ‘Beating Anxiety Together’ project from the NE of England [36], indicates that two thirds of families approached consented to taking part in the research and that attrition during the therapy phase was less than 10 %. Therefore, in order to achieve 30 participants who complete the trial and provide follow-up data, it may be necessary to approach 50 patients.

### Quantitative data and analysis

A database will be designed to facilitate accurate data entry with inbuilt checks, and a proportion of the data entry will be checked. As this is a feasibility study, the analyses of the data collected will be mainly descriptive, with 95 % confidence intervals reported where appropriate.

At baseline, the distribution of all numerical variables will be examined graphically and summarised by appropriate measures of location and spread. Similarly, baseline categorical variables will be tabulated and percentages reported. No formal statistical comparisons between treatment arms will be made; any comparisons will be descriptive and exploratory. Confidence limits for the estimated standard deviations of key study parameters will be calculated and used in sensitivity analyses for sample size calculations for a future multi-centre RCT study application.

### Qualitative data and analysis

Semi-structured interviews with young people and family members in the trial will be employed to gather their individual views in detail, while a focus group will allow trial participants to feed back on the findings from the individual interviews, and provide socially constructed perspectives to contrast with individual ones. Employing both methods will enable the participation of both those who may feel inhibited by group discussion and those unable or unwilling to attend interviews.

We will purposively sample families (*n* = 15), including three families in the control condition, seeking a representative male/female ratio and diversity in terms of age, diagnosis and time since diagnosis, family members and size. An attempt will be made to interview 2 family members within each family either face to face at the University, at home or by telephone by a qualitative researcher, giving a sample of 30 participants. Interviews will commence after 6 months following the last session of the intervention, with each interview expected to last approximately 45 min. Since it will also be important to feasibility to know why families may not wish to take part in the intervention or research, we will also invite a member from each of 5 families refusing participation to consent to a brief telephone interview on a voluntary basis to raise concerns they may have had. The interview agendas will initially be developed by members of the Project Advisory Group (PAG) including our parent and young people representatives to cover areas of research interest (attitudes towards and experiences of both the intervention and research procedures). The agenda will be flexible to allow both expected and emergent themes to be incorporated into later interviews [37].

Both interviewees and family members who were not interviewed will be invited to a focus group intended to provide feedback on the initial findings and gain the families’ perspectives on the outcomes of analysis. The focus group discussion will be structured around a presentation of the initial findings, thus allowing both interviewees and non-interviewees with comparable circumstances to comment on how these represent the experience and attitudes of families affected by BD in general and increase confidence in the broader applicability of findings [38]. Interviews and the focus group will be tape-recorded, with participant’s written consent, transcribed, anonymised and subjected to framework analysis [39]. This is an appropriate approach for qualitative health research with objectives linked to quantitative investigation [40]. We will use NVivo to aid indexing and charting. The data will be repeatedly read and coded independently by two researchers to increase the reliability of the study. When discrepancies between coders exist, these will be discussed until a consensus is reached. Analysis will be discussed at regular meetings of the research team in order to identify areas for closer consideration (including negative case analysis) and to enhance credibility of the thematic framework and interpretation [38]. Figure 1 shows a flow diagram from the feasibility study.

